
## Methods

### Study Design

This study is a multicenter uncontrolled intervention trial (iHand). All participants will be assessed 5 times: 3 preassessments, 1 postassessment, and 1 follow-up assessment (Figure 1). SPIRIT (Standard Protocol Items: Recommendations for Interventional Trials) [28] will be used.

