A diary will be kept daily by the participants during the 6-week intervention period. Participants will be asked to report how often and for how long they use the Carbonhand system each day, when they use the system (morning, afternoon, evening), and during which activities. Information from the diaries will be transcribed by the investigator. The study coordinator will perform thematic analyses on those transcriptions to extract qualitative information about glove use and participants’ experiences using the Carbonhand system.

A semistructured qualitative interview with open-ended questions will be performed by the investigator at the T3 assessment, to collect participants’ experiences about using the Carbonhand system in daily life and the user-friendliness of the system. The interview will last approximately 15 minutes and was developed by Roessingh Research and Development BV in collaboration with Bioservo with the aim of learning about the user experiences and to improve the Carbonhand system. Data extraction (written answers of the interview) will follow the same procedure as that used for the diaries.

If a participant withdraws from the study during the intervention period, we will aim to obtain the reason for stopping, the maximum handgrip strength, and glove-use data and to complete the semistructured interview.

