### Statistical Analysis

Outcome measures will be analyzed using SPSS statistical software (version 19; IBM Corp). Data from the 3 baseline assessments (T0, T1, and T2) will be averaged (for overall preassessment values). Statistical analysis of the therapeutic effect will be performed on all participants who completed all assessments up to and including T3 and T4. Data from participants who drop out before or during the intervention period will be analyzed separately to analyze the patient characteristics of dropouts, including the reasons for dropout, to identify potentially relevant information regarding reevaluation of target population, device-related issues, to inform proper interpretation of study outcomes.

Normality of data distribution for each outcome measure will be checked by visual inspection and with the Shapiro-Wilks test, prior to analyzing outcome measures. Descriptive statistics will be used for all outcome measures (mean and standard deviation or median and interquartile range as applicable). The overall level of significance will be set to *P*<.05.

In order to assess the effect of the intervention over time, linear mixed models will be used to analyze changes in outcome measures over time. If a significant difference is found between sessions, multiple comparisons are performed with Sidak posthoc analysis. If data are not normally distributed, logarithmic transformation will first be applied to potentially achieve normally distributed data and enable use of linear mixed models for analyses. Otherwise, the Friedman test will be used for nonparametric analysis.

In addition, correlations (Pearson correlation coefficient or the nonparametric Spearman correlation coefficient, depending on data characteristics) between amount of use (measured by diary, Carbonhand system, or Motor Activity Log) or baseline patient characteristics and change in hand function outcome measures will be calculated to evaluate whether an increased dose or specific patient characteristics are associated with better outcomes

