In addition to these strengths, we face some challenges. First, the therapeutic effects of Carbonhand will be assessed using an uncontrolled design because of practical reasons—limited availability of resources in terms of project funding and project duration. Second, some outcome measures, for example those assessed with the Motor Activity Log, Michigan Hand Outcomes Questionnaire–Dutch Language Version, Short Form 36, EQ-5D, and the semistructured interview and diaries, are self-reported, which includes the risk of socially desirable answering. Potential bias is reduced as much as possible by allowing participants to complete the questionnaires by themselves, without interference from the health care professional. Finally, participants that might be disappointed about the effect of the glove may have a higher risk of dropout during or directly after the intervention period. This may influence postintervention (T3) and follow-up (T4) results. In order to prevent this effect as much as possible, professionals were instructed to explain the importance of completing the study to all participants at the start of the study. In addition, the characteristics of the dropout sample will be analyzed to inform proper interpretation of study outcomes. Another limitation is the cumulative collection of glove-use data via the Carbonhand system. This means that the exact amount of use per day per week or per bout of activity cannot be retrieved. In order to obtain insight into day-to-day use of the glove, participants are asked to note this information daily in a diary.

This is the first powered clinical trial to investigate the unique application of an assistive grip-supporting soft robotic glove for use outside of clinical settings with the aim to have a therapeutic effect. Despite the abovementioned challenges, the study will provide a solid knowledge base about the therapeutic effect of 6 weeks of home use of an assistive grip-supporting glove.

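### Limiting the therapeutic-effect analysis to participants with every assessment through T4 discards usable grip data and, if disappointed participants leave more often, is likely to overstate the effect

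*Protocol article*

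**What the plan says.** The Statistical Analysis section of the protocol article defines who contributes to the main claim: "Statistical analysis of the therapeutic effect will be performed on all participants who completed all assessments up to and including T3 and T4". It describes one other group: "Data from participants who drop out before or during the intervention period will be analyzed separately". The purpose of that second analysis is to describe the dropouts and their reasons for leaving. It does not return them to the effect estimate. The same section averages T0, T1 and T2 into one baseline, and plans that "linear mixed models will be used to analyze changes in outcome measures over time", with the Friedman test as fallback.

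Under Secondary Outcome Measures, for participants who withdraw during the intervention, "we will aim to obtain the reason for stopping, the maximum handgrip strength, and glove-use data". Maximal handgrip strength is the primary outcome. Study Procedure places T4 four weeks after T3, to measure retention.

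The Discussion names the risk: "participants that might be disappointed about the effect of the glove may have a higher risk of dropout during or directly after the intervention period". It adds: "This may influence postintervention (T3) and follow-up (T4) results". Its two responses are to explain to participants why completing the study matters and to describe the dropout sample. Study Design states that there is no comparator: "This study is a multicenter uncontrolled intervention trial (iHand".

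**The concern.** T4 measures retention, yet having T4 becomes a condition for contributing to the T3 comparison. A participant measured at T3 who does not return for T4 is lost from both. That participant is not in the dropout group either, because that group ends with the intervention period, so the two described groups do not cover everyone. Read literally, one missed baseline visit also excludes a participant, although the baseline is an average of three.

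The people most exposed to this rule are those whom the Discussion singles out: participants who leave during or directly after the intervention because the glove disappointed them. If disappointment goes with smaller gains in grip, the rule removes low changes from the average. In a controlled trial, similar loss in the other arm might offset part of this. Here the mean change is the effect estimate, so any selection passes straight into it. Describing the dropouts helps a reader interpret the result but does not alter it.

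The rule also works against the rest of the plan. A linear mixed model accepts incomplete records, and the plan seeks the primary outcome at withdrawal but gives it no place in the effect analysis.

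**Working it through.** **Inputs from the Sample Size section:** expected improvement 2.16 kg, SD 5.2 kg, 56 evaluable participants, 10% dropout, 63 enrolled.

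**Plan's own figure.** 56 / (1 − 0.10) = 62.2, rounded up to 63; this reproduces. The allowance protects power. It does nothing about bias if those who leave differ from those who stay.

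**Assumption.** The documents give no figure for how dropout relates to change in grip. Suppose each participant has an unobserved tendency to drop out, normally distributed, with correlation r to poor change, and that the fraction f with the highest tendency leaves. The r here is a latent correlation. The correlation with actual dropout (yes/no) is smaller: at f = 0.10, r = 0.5 corresponds to 0.5 × 0.1755 / √(0.10 × 0.90) = 0.29.

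**Formula.** Excess of the completer mean over the mean of all participants = SD × r × φ(z) / (1 − f), where z is the (1 − f) normal quantile.

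**At the planned 10%.** z = 1.2816 and φ(z) = 0.1755, so the excess is 5.2 × r × 0.1755 / 0.90 = 1.014 × r.

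| r | Excess (kg) | Share of 2.16 kg |
|---|---|---|
| 0 | 0 | 0% |
| 0.1 | 0.10 | 5% |
| 0.2 | 0.20 | 9% |
| 0.3 | 0.30 | 14% |
| 0.5 | 0.51 | 23% |

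The limit, in which exactly the worst 10% leave, is 1.01 kg.

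**At 20%, illustrative only (the plan gives 10%).** φ(z) = 0.2800, so the excess is 5.2 × r × 0.2800 / 0.80 = 1.820 × r: 0.55 kg at r = 0.3 and 0.91 kg at r = 0.5.

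**Cross-check with a different dropout model.** At 10% loss and no true mean change, if the odds of dropout double per SD of worse change, the completer mean is about +0.35 kg. If the odds quadruple, it is about +0.61 kg.

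**Second view, fixing the dropouts' mean change m.** If completers improve by 2.16 kg and 10% leave, the mean over everyone is 0.9 × 2.16 + 0.1 × m = 1.944 + 0.1m.

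| m (kg) | Mean over everyone (kg) | Completer excess (kg) |
|---|---|---|
| 1.08 | 2.05 | 0.11 |
| 0 | 1.94 | 0.22 |
| −2.16 | 1.73 | 0.43 |

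**How much the mixed model alone repairs.** Take dropouts who contribute only a baseline, equal SDs at both times, and an assumed baseline-to-post correlation of 0.8 to 0.9. The squared correlation between baseline and change is (1 − 0.8)/2 = 0.10 to (1 − 0.9)/2 = 0.05. If dropout depends on the change itself, baseline data therefore remove only about 5% to 10% of the excess: 0.51 kg becomes about 0.46 to 0.48 kg. The real gain comes from T3 values of participants without T4 and from grip measured at withdrawal.

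**The case against.** Four objections deserve weight.

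*Certainty.* A reader might infer that the protocol expects disappointed dropouts and that the effect is therefore biased upward. The Discussion does not go that far. It says only that such participants may be more likely to leave and that results may be influenced, and it gives no direction. Disappointment is a perception, whereas the primary outcome is a dynamometer reading without the glove; nothing in the documents links the two. This stands: upward bias is the likely direction under the protocol's premise, not an established fact.

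*Reading.* The phrase about T3 and T4 could mean completion to T3 for the post-intervention comparison and to T4 for follow-up. The dropout group, which ends with the intervention, fits that reading. It strains the sentence, however, and would still exclude everyone who leaves during the intervention. The ambiguity is itself a reason to rewrite.

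*Type I error.* A reader might also want to quote an inflated false-positive rate. A one-sample t-test with no true change, 10% loss and 57 completers gives one-direction rates of 6.4% at r = 0.3 and 10.8% at r = 0.5, instead of 2.5%. The plan specifies a mixed model across sessions with Sidak comparisons only after a significant session effect, so these are not the error rates of the planned test.

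*Disclosure.* The limitation is acknowledged, retention is encouraged, and reasons and grip are sought at withdrawal. That is to the plan's credit, but none of it changes the estimate.

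**Conclusion.** The point holds in a limited form. The completer rule is explicit, and nothing in the article returns T3-without-T4 participants, dropouts or the withdrawal grip value to the effect estimate. Under the Discussion's premise, and without a control arm, the estimate is likely to be too high.

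The size cannot be determined from the documents. At the planned 10% loss with SD 5.2 kg it runs from 0 kg (dropout unrelated to change) to about 0.5 kg (latent correlation 0.5), against 2.16 kg. The correlations are assumptions. At 10% loss the distortion is modest for most of that range; larger figures need either heavier loss than planned or a stronger link between response and dropout.

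**What to change.** Replace the completer sentence before the database is locked, along these lines:

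- **Primary analysis:** the planned linear mixed model on all participants who received the glove and have at least one baseline grip value, using all available assessments. T3 does not depend on T4.
- **Baseline:** state how it enters the model, either as the mean of the available T0–T2 values or as separate visits. If separate visits replace the averaged baseline, say so openly.
- **Withdrawal grip:** where obtained, include it as the post-intervention value under a stated assignment rule, since it is measured at an unscheduled time.
- **Completers:** keep them as a sensitivity analysis and for the Friedman fallback, which needs complete records.
- **Outcome-related dropout:** add a sensitivity analysis that gives dropouts without post data zero change and also a range of worsening. Zero change alone is not conservative if dropouts deteriorated.

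No new data collection is needed. The cost is a change of wording, a little more analysis work and, probably, a slightly less favourable estimate.

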### Study Procedure

All health care professionals involved in the study received extensive training prior to the start of the patient recruitment in order to standardize the execution of the study across the different centers. Plenary instruction sessions were scheduled; health care professionals were trained in good clinical practice, execution of the study protocol, in fitting and operating the Carbonhand system, and in explaining (following a standard procedure) the use of the Carbonhand system to the participants. All instructions were also documented in logbooks and manuals, which were provided to the professionals. The latest versions of these documents are maintained on a secure project website.

In total, there are 5 assessments for each participant. Three preassessments (T0, T1, and T2) are scheduled across 3 weeks, as baselines, directly prior to the intervention period. After completing the third baseline session, the Carbonhand system is manually adjusted by the professional to the individual participant. Attention is paid to the correct size of the glove and arm straps, the finger length of the glove, and creating 3 support profiles. In addition, instructions about all aspects of the Carbonhand system are given, demonstrated, and practiced with the participant, until the professionals are confident that the participant knows how to use the system properly at home. In addition to receiving the Carbonhand system, all participants will be provided with a short user manual (in Dutch) and an excerpt from the exercise book [30], in which exercises (functional activities that can be used in the home situation) are described for people with almost complete function of the arm.

During the 6-week intervention period, participants use the Carbonhand system at home. Within 1 week of the end of the intervention period, postassessment (T3) is conducted; 4 weeks later, a follow-up assessment (T4) is conducted, to measure the retention of effects.

Monitoring visits by an independent study monitor are planned for each participating center to ensure the continued protection of participants rights and well-being, to assure protocol adherence, and to verify data integrity during the study in compliance with good clinical practice. All protocol deviations will be filed. We anticipate having 5 monitor visits to each center during the course of the study.

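### Participants who leave after the glove period but before T4 fall outside both the effect analysis and the dropout analysis, although the protocol names such dropout as a risk to T3 and T4

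*Protocol article*

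**What the plan says.** All of this is in the protocol article; no separate analysis plan is at hand.

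- **Statistical Analysis, effect analysis:** "Statistical analysis of the therapeutic effect will be performed on all participants who completed all assessments up to and including T3 and T4".
- **Statistical Analysis, dropout analysis:** "Data from participants who drop out before or during the intervention period will be analyzed separately". The aims include describing these people and their reasons for leaving, so that outcomes can be interpreted properly.
- **Secondary Outcome Measures, last paragraph:** "If a participant withdraws from the study during the intervention period, we will aim to obtain the reason for stopping", together with grip strength, glove-use data and the interview.
- **Study Procedure, timing:** "Within 1 week of the end of the intervention period, postassessment (T3) is conducted", and "4 weeks later, a follow-up assessment (T4) is conducted, to measure the retention of effects".
- **Discussion, limitations:** disappointed participants "may have a higher risk of dropout during or directly after the intervention period". The text continues: "This may influence postintervention (T3) and follow-up (T4) results". Two responses follow: stressing at the start the importance of completing the study, and a promise that "the characteristics of the dropout sample will be analyzed to inform proper interpretation of study outcomes".

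**The concern.** A completer analysis can be defended only if the people it leaves out are described. Here the rule for the effect analysis and the rule for the dropout analysis do not add up to the whole sample. The uncovered stretch runs from the end of glove use to T4, and it contains the period directly after the intervention that the Discussion worries about.

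The consequence reaches the primary comparison. A participant with three baselines and a T3 grip measurement who misses T4 is excluded from the pre-post change as well as from follow-up. That exclusion occurs after the participant knows how the glove worked out. The trial is uncontrolled, so no comparison arm can show whether the selection matters. If disappointed people leave and their grip gained less, the completer mean is shifted in favour of the glove, and nothing in the stated plan would describe who they were.

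A second, smaller mismatch concerns reasons for leaving. They are to be analysed for exits before or during the intervention, but the protocol states an aim to obtain them only for exits during it.

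**Working it through.** **Step 1. Set the rules side by side by time of leaving.**

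| Time of leaving | In effect analysis | In dropout analysis | Reason sought | Named as a risk in Discussion |
|---|---|---|---|---|
| Before the glove period | no | yes | no | no |
| During the glove period | no | yes | yes | yes |
| End of glove period to T3 | no | no | no | yes |
| T3 to T4 | no | no | no | yes, if directly after |
| Completed all visits to T4 | yes | not applicable | not applicable | not applicable |

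Rows three and four are the gap. Row one shows the mismatch on reasons.

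**Step 2. Length of the gap.** Inputs from Study Procedure: 3 weeks of pre-assessments, 6 weeks of glove use, 0 to 1 week to T3, then 4 weeks to T4.

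- Total schedule: 3 + 6 + 0 + 4 = 13 weeks, to 3 + 6 + 1 + 4 = 14 weeks.
- Gap, counted from the end of the glove period: 4 to 5 weeks.
- Share: 4/13 = 31% to 5/14 = 36%.

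The extension of the glove period allowed under Intervention would lengthen the total and lower the share somewhat.

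**Step 3. Number of people.** Inputs from Sample Size: 56 needed, 10% dropout, 63 to enrol. The plan's figure reproduces: 56/(1 − 0.10) = 62.2, rounded up to 63. The allowance is 63 − 56 = 7 people. If leaving is spread evenly over the schedule (an assumption), 7 × 0.31 = 2.2 to 7 × 0.36 = 2.5, so about 2 of 7.

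**Step 4. Possible shift in the T3 result (illustration only).** Assume 56 attend T3, their mean gain is the planned 2.16 kg, and those who then miss T4 gained 0 kg. The mean among the rest is 56 × 2.16/(56 − k) = 120.96/(56 − k).

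- k = 2: 120.96/54 = 2.24 kg (+4%)
- k = 3: 120.96/53 = 2.28 kg (+6%)
- k = 6: 120.96/50 = 2.42 kg (+12%)

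If leavers gained as much as the others, the shift is zero.

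**Step 5. Power.** For a two-sided paired t test at 0.05 with the planned 2.16 kg and SD 5.2 kg, power is 0.863 with 56 analysed, 0.850 with 54, 0.843 with 53 and 0.821 with 50. The first value exceeds the planned 0.80 because this test needs only 48 participants; how the plan reached 56 is a separate matter and is not used here. Losing a few people before T4 does not put power at risk. The issue is selection and unaccounted participants.

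**The case against.** Several points can fairly be made for the protocol.

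- **The wording on T3 and T4 may be meant per visit:** T3 completers for the T3 result, T4 completers for T4. On that reading, people who leave after T3 stay in the T3 comparison. As written, though, both visits are required. The ambiguity is itself a reason to fix the sentence, and the dropout analysis would still omit these people at T4.
- **The Discussion gives no window for its dropout sample**, so it may have been meant broadly. This is possible, but Statistical Analysis is the only place that defines the group, and it stops at the end of the intervention.
- **A reader might infer three competing definitions of dropout.** The text does not support that. The withdrawal paragraph is a data-collection rule for people who stop mid-intervention. For anyone who attends T3, everything on its list except the reason is already collected. Only Statistical Analysis defines an analysis group.
- **A reader might infer that late leavers affect only the retention result.** The completer rule removes them from T3 too.
- **A reader might infer that half or more of all dropouts could be missed.** No figure in the protocol supports this.
- **A reader might object that run-in leavers are mixed with glove users.** The protocol does not say the two are pooled, and run-in leavers bear on its stated aim of re-evaluating the target population.
- **This is a condensed article**, and exit forms and dropout tables are commonly left to fuller documents. That would excuse silence. It does not excuse a stated window that misses the stated risk.

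It also stands that the numbers are small: comparing about two leavers with everyone else can only be descriptive.

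**Conclusion.** The point holds as a gap between two adjacent rules and the purpose the protocol gives them. Read as written, anyone who leaves between the end of glove use and T4 is in neither analysis, and the T3 comparison loses usable data. The mismatch on reasons for leaving before the intervention also holds.

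The size is modest: 31 to 36% of the schedule and about 2 of 7 expected dropouts. This rests on the 10% allowance and an even spread over time, neither of which is an observed rate for this period. The effect on power is slight. Any bias in the mean change would favour the glove if disappointed participants leave and gained less; its size is unknown, and the 4 to 12% in the working is illustrative. The plan should be corrected, mainly so that every enrolled participant is accounted for and the T3 result does not depend on attending T4.

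**What to change.** 1. In Statistical Analysis, define the dropout analysis as any exit before T4, and report it by timing: before, during or after the glove period. Describe those who leave after T3 by baseline characteristics, T3 grip change and registered glove use, all of which are already collected by then.
2. In the withdrawal paragraph of Secondary Outcome Measures, ask for the reason at every exit.
3. State that the T3 comparison uses everyone with T3 data. The planned linear mixed model allows this, and it can take account of dropout that depends on the observed T3 grip. Keep T4 completers as a sensitivity analysis. The Friedman fallback needs complete rows, so on that route the T3 comparison would need its own paired analysis.

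The cost is one descriptive table, one exit question and changed wording in two sections, with no new visit or participant. The protocol article reports 52 enrolled by October 2021 and the study still running in March 2022, so the question can be put only to future leavers. The Ethics section requires committee approval of the amendment. With so few people expected, the table should be read as description and not as a test.

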### Participants

We aim to enroll patients with chronic perceived hand function problems, including decreased handgrip strength. Since this impairment is caused by a wide range of disorders, such as acquired brain injury, osteoarthritis, rheumatoid arthritis, spinal cord injury, orthopedic problems or other neurological disorders, we have chosen not to limit the study to a single disorder but rather to focus on the common motor limitation, for which the intervention was developed. Therefore, the study sample is heterogeneous. In each center, a rehabilitation physician or clinical researcher is involved in the identification of potential participants for the study, based on screening of predefined selection criteria. The candidates will be contacted by the professional from that particular center to inform them about the study. When participants are interested, an information letter is sent to them. After 1 week, the health care professional will contact candidates to determine their interest in participating in the study and to answer possible questions. If interested in participating, a physical appointment is scheduled to obtain informed consent form, and then, to complete the screening procedure (some selection criteria require physical tests).

Inclusion criteria are (1) age between 18 and 90 years, (2) being in a chronic and stable phase of disease, (3) having received treatment for limitations in performing activities of daily living due to a decline in hand function (regardless of underlying disorder) at the involved rehabilitation center and department, (4) being capable of at least 10° of active extension of the wrist and fingers and 10° of active flexion of the fingers, (5) having the ability to make a pinch grip between thumb and middle or ring finger, (6) having the ability to put on the glove, (7) having sufficient cognitive status to understand 2-step instructions (judged by personal contact between participant and experienced health care professional), (8) living at home, and (9) providing written informed consent. To ensure that people are able to meet the recommended amount of use, an initial inclusion criterion was that the most affected hand of the participant was the dominant hand; however, due to support of the glove during mainly bimanual activities, this inclusion criterion was removed.

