Jebsen-Taylor Hand Function Test is a reliable and valid test to evaluate functional hand motor skills in different patient groups and healthy people of various ages [37]. The test consists of 7 different unilateral hand skill tasks related to activities of daily living: (1) writing a sentence of 24 characters, (2) turning over 7.6 cm × 12.7 cm cards, (3) picking up and moving small common objects (eg, paper clips, coins, and bottle caps), (4) stacking checkers (test of eye–hand coordination), (5) simulated feeding (eg, teaspoon with beans), (6) picking up large empty cans, and (7) moving weighted (450 g) cans. The duration of each task will be recorded in seconds and summed for the test score [38].

Michigan Hand Outcomes Questionnaire–Dutch Language Version (a total of 57 items) assesses patients’ opinions their hands and health [39,40]. The questions are used to assess out how patients feel and to what extent they are capable of carrying out daily activities in the past week (with the exception of part 3, in which the last 4 weeks is used). The problem is mapped out within 6 domains: total hand function, activities of daily living, work situation, work performance, pain, aesthetics, and satisfaction. Within each domain, items are scored on a 5-point Likert scale. The scores are normalized to a range of 0 to 100. For the pain scale, higher scores indicate more pain. For the other 5 scales, higher scores indicate better performance.

The Motor Activity Log [41] is a semistructured questionnaire that assesses self-perceived amount of use and quality of movement of the affected arm and hand by stroke patients during activities of daily living. This questionnaire consists of 26 activities and has excellent test-retest reliability for both scores of each activity; each activity is rated by the participant for quality of movement and amount of use of the upper extremity on a 5-point scale.

An 11-point numeric pain rating scale—from 0 (no pain) to 10 (the most intense pain imaginable)—is used to measure the subjective intensity of pain (patients select a value that is most in line with the intensity of pain that they have experienced in the last 24 hours). The numeric pain rating scale has good sensitivity, while producing data that can be statistically analyzed [42].

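### A normality check on the outcome data, made before any model is fitted, decides whether the primary result is a kg change, a ratio or a rank test

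*Protocol article*

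**What the plan says.** All of the rule is in the Statistical Analysis section of the protocol article.

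- Gate: "Normality of data distribution for each outcome measure will be checked by visual inspection and with the Shapiro-Wilks test, prior to analyzing outcome measures".
- Default method: "linear mixed models will be used to analyze changes in outcome measures over time", followed by "If a significant difference is found between sessions, multiple comparisons are performed with Sidak posthoc analysis".
- First switch: "If data are not normally distributed, logarithmic transformation will first be applied to potentially achieve normally distributed data", after which the mixed model is used on the log values.
- Second switch: "Otherwise, the Friedman test will be used for nonparametric analysis".
- Baseline: "Data from the 3 baseline assessments (T0, T1, and T2) will be averaged (for overall preassessment values"). I read this as three levels in the model: pre, T3 and T4.

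The rule covers every outcome and makes no exception for handgrip strength. The Sample Size section plans the trial on a mean gain of 2.16 kg with an SD of 5.2 kg. Of the population, the Participants section says: "Therefore, the study sample is heterogeneous".

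**The concern.** Residuals do not exist until a model has been fitted, so a check placed before the analysis can act only on the outcome data. That is not the quantity whose normality matters for a mixed model. Participants are aged 18 to 90 and have many diagnoses, so raw grip strength may be skewed or bimodal for reasons unrelated to the treatment effect.

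If the check fails, the primary analysis leaves the scale on which the trial was sized. After logs the effect is a ratio. After Friedman it is a comparison of ranks with no estimate in kg. Which of the three is reported is not known until the data have been seen, and it depends on a property that the model does not require.

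The log step also meets scores for which it is undefined. The pain scale, for example, runs "from 0 (no pain) to 10 (the most intense pain imaginable").

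**Working it through.** **1. Why the raw data are the wrong target.** Write the score of person i at session j as Y_ij = μ + b_i + τ_j + e_ij. The shape of the raw scores is that of b_i + e_ij. The change from pre to T3 is (τ_T3 − τ_pre) + (e_i,T3 − e_i,pre), and b_i cancels. A mix of ages and diagnoses enters through b_i. It can make raw scores non-normal and leave the changes normal.

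**2. The plan's own figures.** Inputs from Sample Size: gain 2.16 kg, SD 5.2 kg, power 0.80, α 0.05.

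- Paired, normal approximation, two-sided: [(1.960 + 0.842) × 5.2 / 2.16]² = 45.5, so 46. With the t distribution: 48.
- The stated 56 matches 48 / 0.864 = 55.6, where 0.864 is the minimum asymptotic relative efficiency of the signed-rank test. The article names no test, so this is a possible origin, not an established one.
- Dropout: 56 / 0.90 = 62.2, so 63, as stated.
- Power of a paired t-test at n = 56: 86.3%.

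Whatever the origin of 56, the planned effect is a mean change in kg.

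**3. Cost of Friedman when errors are normal.** Asymptotic efficiency against the F test is 3k / [π(k + 1)]. For k = 3 this is 9 / (4π) = 0.716, and 1 / 0.716 = 1.40 times the participants for equal power.

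**4. Simulation of the whole rule.**

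- From the article: n = 56, gain 2.16 kg, change SD 5.2 kg (visit error SD 5.2 / √2 = 3.68), three sessions.
- Assumed: the baseline shapes below; additive normal error; the gain fully held at T4; a switch if Shapiro-Wilk gives P<.05 at any session; logs kept only if all three sessions then pass; Friedman if any value is not positive.
- 4000 runs per scenario. A repeated-measures F test stands in for the balanced mixed model.

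| Baseline (assumed) | Raw rejected | Change rejected | Ends at log | Ends at Friedman | Power, kg model | Power, whole rule |
|---|---|---|---|---|---|---|
| Normal, mean 20, SD 8 | 13.3% | 5.4% | 0.3% | 13.0% | 89.4% | 87.4% |
| 8 + gamma (shape 1, scale 10) | 99.3% | 4.8% | 45.0% | 54.2% | 89.4% | 81.0% |
| 6 + gamma (shape 2, scale 7) | 93.0% | 5.2% | 35.3% | 57.7% | 89.9% | 81.6% |
| Mixture: 60% around 12, 40% around 30 | 98.3% | 5.1% | 9.0% | 89.3% | 89.5% | 78.3% |

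- If half the gain is held at T4, the three non-normal baselines give 64.8–69.0% for the rule against 78.1–79.3% for the kg model. The normal baseline gives 77.3% against 78.8%.
- With no effect (the shape 2 gamma baseline), the rule rejects in 4.9% of trials.
- A second set of skewed or mixed baselines gave raw rejection in 72–94%, change rejection in 4–6%, and power of 79–81% for the rule against 89–90%. With normal baselines the loss there was about 1 point.

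**5. A different error model.** With variability proportional to strength, the rule had 93–95% power against 88% for the kg model. A separate run (lognormal baseline, about the same mean gain, change SD near 5.2) gave 97% against 92%. There the rule ended at Friedman in only 10% of trials, and Shapiro-Wilk rejected the change score itself in 69%.

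**6. Zeros.** log(0) is undefined. By the article's own descriptions, pain (0 to 10) and the Michigan and Short Form 36 scores (0 to 100) can be 0.

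**The case against.** The strongest reply is that the rule is specified in advance, keeps its type I error, and may cost no power.

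- **Power.** This stands in large part. The baseline shapes are assumptions. Normal error added to a skewed or mixed baseline produced at least one impossible, non-positive grip value in 36–65% of trials in the second set of simulations, and this pushes trials towards Friedman. Under proportional variability the rule does better than the kg model. A reader might infer that the rule certainly costs power; the documents give no data shape from which to conclude that.
- **Sample size.** If 56 includes a signed-rank allowance, part of a rank test's cost is already paid. The allowance of 0.864 would not fully cover Friedman's 0.716, and the article does not say that it was made.
- **Trigger.** The article combines visual inspection with Shapiro-Wilk and does not say that one P<.05 forces a switch. If only the pre-value is tested, the share ending at Friedman falls from 68–80% to 42–53% in one set of simulations. This reduces how often a switch occurs. It leaves the wrong target in place, and it does not say how the two checks are combined.
- **Lost participants.** A reader might infer that Friedman discards incomplete participants or that zero scorers are dropped. Neither is supported. The effect analysis is already restricted to those who completed the assessments through T3 and T4, and Friedman is the stated fallback when logs do not serve. Nor does the article give EQ-5D values below 0; it gives only 0 for death and 1 for perfect health.
- **Descriptives.** Means or medians will be reported on either branch, so a description in kg survives. That is not an estimate of the change with its uncertainty.

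**Conclusion.** The point holds as a matter of estimand and interpretation. The article fixes a gate on outcome data before modelling and applies it to the primary outcome, so the data choose between a kg difference, a ratio and a rank test. The planned quantity is a mean change in kg. Because the article states the rule itself, this is not a detail left to an unseen analysis plan.

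The gate can trip often for an irrelevant reason. Under additive normal error with skewed or mixed baselines, raw data failed in 72–99% of simulated trials across both sets, and the change score in 4–6%.

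The size of the power effect is not known. It is a loss of roughly 8 to 11 points under those assumptions with full retention (for example 89.4 − 81.0 = 8.4 and 89.5 − 78.3 = 11.2), a loss of 1–2 points with near-normal raw data, and a gain of about 5 to 7 points under proportional variability (93 − 88 and 95 − 88).

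A reader might go further and call the primary test invalid. The 4.9% rejection rate under no effect, in the one null scenario run, does not support that. The zero-score problem concerns the log step for bounded secondary scores; it does not leave them without a test. The change should be made, but the trial does not stand or fall on it.

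**What to change.** 1. Remove the normality gate on the outcome data.
2. Name the linear mixed model on the kg scale as the primary analysis of handgrip strength, and report the mean change from pre to T3 with its 95% CI.
3. Judge normality and constant variance on the model residuals, mainly by plots.
4. Pre-specify log-scale, bootstrap or signed-rank results as sensitivity analyses that do not replace the primary one.
5. Do not log-transform bounded scores that can be 0, such as pain.

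The cost is a few sentences, with no extra data or participants. The Results section says that the study was still running in March 2022, so at that date the change could still be made before the analysis. There is a small downside: if variability is proportional to strength, the kg model may have somewhat less power than a log model. The log-scale sensitivity analysis would show this.
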